Funding:

Funding is provided by NIH-NIAMS U19AR076737 (Overall PI: [name]; directors of Bio-Behavioral Core: [name] and [name]) under title: UCSF Core Center for Patient-centric Mechanistic Phenotyping in Chronic Low Back Pain (UCSF REACH)

Research Plan and Hypotheses:

This is an exploratory, mechanistic observational study with 30 patients undergoing 8-week pre-post assessment without a control group for proof-of-concept: can mindful interoceptive exposure possibly recover decreased interoceptive awareness AND dysfunctional central pain processing, thereby potentially reducing pain impact?

Hypotheses:

This is a proof-of-concept observational study without rigorous testing of hypotheses. Preliminary hypotheses are:

1) the new brief mindful interoceptive exposure task (MIET) is feasible and is acceptable to patients with chronic low back pain (cLBP) (Primary Outcome)

2) in cLBP patients with low interoceptive awareness (= below average scores on the Multidimensional Assessment of Interoceptive Awareness; MAIA), an 8-week mobile phone-based interoceptive exposure task can increase interoceptive awareness and recover dysfunctional central pain processing (assessed by quantitative sensory testing, QST; and fMRI connectivity) (Secondary Outcome)

3) exploratory hypothesis: Pain intensity (NRS) and pain interference (PROMIS-29) will improve from pre to post intervention.

4) exploratory hypothesis: Improvements in pain intensity and interference will be correlated with changes in MAIA scores, QST and fMRI connectivity.

Specific Aims:

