| \| 1) to determine whether a mobile phone-based 8-week behavioral program of a brief mindful interoceptive exposure task (MIET) is feasible and acceptable to patients with cLBP.  2) to determine whether MIET can increase below-average interoceptive awareness (as assessed by the MAIA) in patients with cLBP. We will offer the MIET to the participants in the cohort studies of the BACPAC REACH study (U19) living in the Bay Area, applicants of the Intensive Pain Rehabilitation Program at the VA, and other patients with cLBP, and validate it on self-report outcomes (pain intensity/ interference) *and* objectively (QST and fMRI**)**with 30 participants over 8 weeks, who fit a low interoceptive awareness phenotype.  3) To assess potential changes in chronic pain-related attitudes, believes and coping styles secondary to the intervention. In addition to psychological questionnaires, we will use qualitative exit interviews in 20 selected participants to explore phenomenological differences in patients' attention styles that may be associated with benefits for pain scores.  4) to assess whether potential changes in self-reported pain outcomes and/or objective QST measures are correlated with potential changes in interoceptive awareness (MAIA). All 30 participants will undergo pre-post assessment of pain intensity (NRS), pain interference (PROMIS-29), and QST.  5) to assess whether changes in self-reported interoceptive awareness (MAIA) are associated with changes in brain activity and connectivity. All 30 participants will undergo pre-post assessment of the MAIA and the fMRI Anticipation/Attention task. \| \| --- \| |
| --- | --- |

Design:

This is an uncontrolled, exploratory, mechanistic observational pilot study without control group for the validation of a behavioral task in individuals with chronic pain.

All subjects undergo:

1) questionnaire tests

2) psychophysical testing of cutaneous thermal sensitivity. Using previously validated procedures, we will examine each participant's sensitivity to temperature stimulation.

3) Functional Magnetic Resonance Imaging (fMRI) on the brain.

4) daily pain assessments by electronic momentary assessments (EMA) over 8 weeks

Background and Significance:

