**Analysis of fMRI data:** All structural and functional image processing will be done with the Analysis of Functional Neuroimages (AFNI) software package (or similar) as has been done before by [name] (e.g., Strigo et al., 2013, 2014)^7,8^. Descriptive statistics [M(SD)] of different groups and between group comparisons will be used. All structural and functional image processing (fMRI) and analysis will be performed with the Analysis of Functional Neuroimages (AFNI), FSL, ANTS or similar software packages (Cox, 1996). In order to minimize motion artifact, exoplanar images will be realigned to individually chosen base scan. Additionally, data will be time-corrected for slice acquisition order. Time series data for each individual will be analyzed using a multiple regression model. Data of each subject will be normalized to Talairach coordinates (Lancaster et al., 2000) and a whole-brain mask will be applied to screen out non-brain voxels and voxels falling within the artifact region. The voxel-wise percent signal change data will be entered into a linear mixed effects model or ANOVA with condition as a fixed factor and subjects as a random factor. A threshold/cluster method will then be applied, and the average percent signal difference extracted from regions of activation found to survive this threshold/cluster method.

***Task-based fMRI:***Preprocessed data will be further analyzed with Analysis of Functional NeuroImages (AFNI) software package and optimized based on HCP recommendations. A multiple regression model corrected for autocorrelation consisting of regressors for anticipation and stimulation will be applied to preprocessed time-series data for each individual. For multivariate analysis, a separate regressor will be calculated for each anticipation and stimulation trial such that each event has its own estimated amplitude. To reduce the false positives induced by cross-correlations, time-series data will be fit using the AFNI program 3dREML or 3dLSS to improve classification accuracy.

*Activation maps will be created on a single-subject basis*. Masks of selected ROIs will be created in MNI space using AFNI and will be applied to the functional activation maps using 3dDeconvolve. Using a separate AFNI program, 3dROIstats, the mean activation will be extracted and T-statistics will be calculated in each region to improve classification accuracy.

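### As written, the group-level fMRI model has no Visit 1 to Visit 4 term and no connectivity measure, so it does not estimate the fMRI part of the secondary outcome

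*Protocol*

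**What the plan says.** **The question is change in one group.** Hypothesis 2 (Research Plan and Hypotheses) is that the eight-week task can raise interoceptive awareness and "recover dysfunctional central pain processing (assessed by quantitative sensory testing, QST; and fMRI connectivity) (Secondary Outcome". Hypothesis 4 relates improvement in pain to changes in MAIA, QST and fMRI connectivity. Aim 5 (Specific Aims) relates MAIA change to change in brain activity and connectivity, and states: "All 30 participants will undergo pre-post assessment of the MAIA and the fMRI Anticipation/Attention task". The Research Plan describes "30 patients undergoing 8-week pre-post assessment without a control group". Under Procedures, Visit 4 repeats the Visit 1 scan.

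**The analysis.** Under Analyses, the subsection Analysis of fMRI data enters voxel-wise signal change into a "linear mixed effects model or ANOVA with condition as a fixed factor and subjects as a random factor". The Overall Analysis Approach adds sex and age as covariates. The fMRI subsection also says: "Descriptive statistics [M(SD)] of different groups and between group comparisons will be used". The Task-based fMRI paragraph then extracts mean activation per region for each subject. The following paragraph applies LASSO within each subject to separate task conditions, its example being anticipation of high versus low pain.

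**Template space.** The general pipeline says "Data of each subject will be normalized to Talairach coordinates". The task-based paragraph says "Masks of selected ROIs will be created in MNI space using AFNI and will be applied to the functional activation maps".

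**The concern.** A pre-post question needs a parameter, or a defined contrast, for the difference between visits. The protocol names the fixed and random factors of its model and leaves out visit, the one factor the design turns on. It also names connectivity in two hypotheses and one aim but describes only activation and classification, and it announces group comparisons in a study with one group.

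At stake is the fMRI half of the objective part of hypothesis 2, together with the change measure that hypothesis 4 and Aim 5 need. If neither the change contrast nor the connectivity measure is fixed beforehand, the analyst has to choose both later, possibly after seeing the data. With about 30 participants and many possible regions and contrasts, that freedom matters even in exploratory work.

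**Working it through.** There is no sample size or power figure behind this point to reproduce. The check sets the passages side by side and then asks what the stated model can estimate.

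**1. Sessions and groups.** One group; two scans per participant (Specific Aims; Procedures, Visits 1 and 4). Scans: 30 × 2 = 60. With the 10% attrition assumed under Statistical Design and Power, 27 × 2 = 54 scans come from participants with both visits.

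**2. Terms in the model.** Fixed: condition. Random: subject. Covariates: sex and age. No sentence in Analysis of fMRI data, Task-based fMRI or the LASSO paragraph names session, visit or time, or forms a post-minus-pre difference.

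**3. Meaning of condition.** The fMRI subsection does not define it. The LASSO paragraph uses the word for levels of anticipated pain within the task. That is the natural reading for the group model too.

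**4. What the model returns if both visits enter it.** Let the signal be

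y = subject + b·C + s·T + g·C·T,

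with C = 0/1 for task condition and T = 0/1 for Visit 1/Visit 4. In balanced data a model with only subject and C estimates the condition effect averaged over visits:

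[b + (b + g)] / 2 = b + g/2.

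It has no estimate of s or g. A noise-free least-squares run with 27 subjects, two conditions and two visits confirmed this. The effect sizes are illustrative assumptions, not protocol figures; b = 0.40 throughout.

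| True s | True g | Condition + subject model | With session and condition × session |
|---|---|---|---|
| 0.5 | 0 | condition 0.40 | 0.40, 0.5, 0 |
| 0 | +0.5 | condition 0.40 + 0.25 = 0.65 | 0.40, 0, +0.5 |
| 0 | −0.5 | condition 0.40 − 0.25 = 0.15 | 0.40, 0, −0.5 |

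A uniform shift between visits leaves no trace in the condition estimate. A change in the condition effect is blended into one average. Adding the two terms recovers every effect.

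**5. If each visit is modelled separately.** The model then gives b at Visit 1 and b + g at Visit 4, but still no stated comparison of the two. The gap is the same under either reading.

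**6. Connectivity.** The measures described are percent signal change, regional mean activation and classification of task conditions. None is a connectivity measure, so repairing the activation model alone would not address the outcome as worded.

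**7. Groups.** The Design section says: "This is an uncontrolled, exploratory, mechanistic observational pilot study without control group". The protocol does name subsets elsewhere: the upper and lower terciles chosen for exit interviews, and those who answer 70% or more of phone prompts. The fMRI text refers to neither.

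**The case against.** **Can the fMRI outcome be delivered at all?** A reader might infer that it cannot, and that no individual change score will exist. The documents do not support that. Regional means are extracted for each subject, the same scan is done at both visits, and subtracting one from the other gives a change score. Hypothesis 4 and Aim 5 show that such a score is intended. What is missing is a written contrast, not the ability to form one.

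**Pooling is inferred.** The protocol does not say that both visits enter one model, and the task meaning of condition rests on an example given for a separate step. This is fair. The least-squares run shows only what follows if the visits are pooled; it is not evidence of intent. But the separate-visit reading leaves the same gap, and stretching condition to include visit needs words that are not there.

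**It belongs in the SAP.** A SAP may exist, and a detailed connectivity pipeline could reasonably sit there. The model's factors are different: the protocol states them and omits one the design needs.

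**Misplaced masks.** A reader might infer from the two coordinate systems that regional values would come from the wrong tissue. The two statements sit in separate paragraphs, and one unstated transform would reconcile them. This is a wording inconsistency to tidy.

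**Circularity.** A reader might also object to extracting signal from clusters that survived thresholding. That is not shown to bias the pre-post estimate. Clusters selected on condition averaged over visits are selected on a contrast that is orthogonal to change in balanced data, and the protocol does not say that effect sizes for change will come from those clusters.

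**The study is exploratory.** Feasibility and acceptability are primary, and the protocol disclaims rigorous hypothesis testing. This lowers the severity but does not supply the missing contrast.

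**Conclusion.** The point stands at moderate severity. As written, the analysis does not estimate the change from Visit 1 to Visit 4, describes no connectivity measure for an outcome defined by connectivity, and promises group comparisons without defining groups. It touches all fMRI pre-post inference (up to 60 scans) and the fMRI correlations in hypothesis 4 and Aim 5. It does not touch the feasibility outcome, QST or the questionnaires, and no data are lost.

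The conclusion assumes that condition means task condition, which is likely but not certain, and that no other text, such as an unseen SAP, adds the contrast. The connectivity and group points do not depend on the first assumption. The Talairach/MNI difference is a minor item to reconcile and carries no weight in this verdict.

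**What to change.** 1. **Model.** Add session (Visit 1, Visit 4) and condition-by-session to the fixed effects. Keep sex and age as covariates and subject as a random effect. A paired post-minus-pre contrast for each condition would serve equally well.
2. **Change measure.** Name that contrast, taken from the pre-defined ROI masks, as the fMRI change measure, and state that it is the quantity to be related to MAIA change.
3. **Connectivity.** Either state a connectivity measure and analyse it with the same session contrast, or replace connectivity by activation in hypotheses 2 and 4 and bring Aim 5 into line.
4. **Groups.** Define the groups meant by the between-group sentence, or delete it.
5. **Template space (minor).** State one space for data and masks, or the transform between them.

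The cost is analysis wording and scripting. No new data, visits or participants are needed. The text should be settled before the fMRI data are analysed.

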**Statistical Design and Power**: The primary purpose of this study is to determine feasibility and validate a novel mindfulness and interoceptive exposure-based intervention (MIET) in a subtype/phenotype of cLBP patients with low (below average) interoceptive awareness to determine initial clinical utility as a basis for future research. To achieve this, we will offer the MIET to the participants in the UCSF REACH Clinical Core cohort and the IPRP program at the SFVAMC, validate it on self-report outcomes (pain impact) *and*objectively (QST and fMRI Anticipation/Attention task à BBC proposal**)** with 30 participants over 8 weeks, who fit a low interoceptive awareness phenotype. Statistical power was estimated based on feasibility to find significant changes in disability outcomes (primary outcome, pain impact at 8 weeks.

In a very first pilot study of MIET in Australia participants experienced a significant reduction in pain intensity with a standardized effect size of *d*=1.37.1 This report may be overly optimistic. Assuming 10% attrition, we would be able to detect a ES *d*=0.78 (two-tailed; alpha 0.05, beta 0.2). For these preliminary estimations of the effect size, we used power calculations on the basis of the normal approximation with a 5% significance level for a 2- sided test, we determined that a sample size of 30 patients would provide adequate power (.70–.93) to detect minimal clinically important change. As this is a proof-of-concept study rather than an efficacy study, we will primarily assess for standardized effect sizes (Cohen’s *d*with 95% confidence intervals).

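### fMRI signal is extracted from clusters that passed a whole-brain threshold in the same participants, so an effect size for the contrast that selected them would be biased upward

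*Protocol*

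**What the plan says.** **Selection and extraction** (Protocol, Analyses, Analysis of fMRI data). The search space is the whole brain: "a whole-brain mask will be applied to screen out non-brain voxels". Voxel-wise percent signal change goes into a "linear mixed effects model or ANOVA with condition as a fixed factor and subjects as a random factor". No time or session factor is named. After thresholding, the plan takes "the average percent signal difference extracted from regions of activation found to survive this threshold/cluster method". It names no split sample, separate localiser or other independent data for this step, states no voxel or cluster threshold, and does not say what the extracted averages are for.

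**Second route** (Task-based fMRI, same section). "Masks of selected ROIs will be created in MNI space using AFNI", and mean activation is taken from them. How and when these regions are selected is not stated. The regional averages then feed the single-subject LASSO models.

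**How results are summarised** (Statistical Design and Power). The protocol says "we will primarily assess for standardized effect sizes", as Cohen's d with 95% confidence intervals. The sentence is general: it is not limited to pain and does not exclude fMRI.

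**Rank of fMRI** (Research Plan and Hypotheses; Specific Aims). Feasibility and acceptability are the primary outcome. The second hypothesis, labelled secondary, is that the task can "recover dysfunctional central pain processing (assessed by quantitative sensory testing, QST; and fMRI connectivity) (Secondary Outcome"). Aim 5 relates MAIA change to change in brain activity and connectivity, which needs a brain value for each participant.

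**The concern.** A d and its usual interval assume that the region was fixed before the data were seen. Here the region is found by searching the brain for places where the difference is large relative to its noise. The average is then taken from the same participants in those same places. For the selecting contrast, the estimate is conditional on having passed a significance threshold, so small values cannot appear.

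Three things make this more than a missing detail. The extraction rule is written into the plan. The general effect-size sentence allows a d and CI to be attached to the extracted values. And the study is meant as a basis for later research, so an fMRI d that cannot be small could mislead the planning of the next study. There is no control group, so nothing in the design would expose a change produced by selection.

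**Working it through.** **The plan's own figure.** There is none for fMRI. The only precision figure, a detectable d of 0.78, is tied to "primary outcome, pain impact at 8 weeks" and does not enter this check.

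**Inputs.** From the protocol: 30 participants and 10% attrition, so 30 × 0.9 = 27 completers; single group, pre-post. Assumed, because no threshold is given: two-sided voxel p<0.001, with p<0.005 and p<0.01 as the range; clusters of at least 20 voxels in the spatial simulation.

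**Step 1: smallest d that can survive at a voxel.** For a one-sample t with n = 27, |d| must exceed t(crit, 26 df)/√n.
- p<0.001: 3.707/√27 = 3.707/5.196 = 0.71
- p<0.005: 0.59
- p<0.01: 0.53

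**Step 2: expected d given survival.** Simulate t = (Z + d√n)/S, with Z standard normal and S² a chi-square on 26 df divided by 26. Keep draws with t above the threshold and average t/√n (400,000 draws per cell). Coverage uses d̂ ± 1.96·√(1/n + d̂²/(2n)).

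| True d | Mean d, p<0.001 | Ratio | CI coverage | Mean d, p<0.01 | Ratio | CI coverage |
|---|---|---|---|---|---|---|
| 0.2 | 0.80 | 4.0 | 0% | 0.64 | 3.2 | 52% |
| 0.3 | 0.81 | 2.7 | 9% | 0.65 | 2.2 | 80% |
| 0.5 | 0.85 | 1.7 | 84% | 0.70 | 1.4 | 94% |
| 0.8 | 0.95 | 1.18 | 96% | 0.86 | 1.08 | 97% |
| 1.0 | 1.07 | 1.07 | 97% | 1.04 | 1.04 | 96% |

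With no true effect, the mean |d| among survivors at p<0.001 is 0.79.

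**Step 3: cluster averages.** A smooth two-dimensional field, n = 27, p<0.001, at least 20 voxels, 150 replicates. The d in each surviving cluster is compared with the d in the same cluster from independent data.
- Voxel d 0.3: 1.07 against 0.39, ratio 2.7 (about 0.1 × 150 = 15 clusters, so imprecise)
- Voxel d 0.5: 1.17 against 0.68, ratio 1.7
- Voxel d 0.8: 1.65 against 1.44, ratio 1.15

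An unrelated contrast with no true effect, measured in the same clusters, gave 0.02, 0.02 and 0.00: no inflation.

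**Step 4: what this means for pre-post change.** The selecting factor is called condition and is not defined further. There are three possible readings:
- *Clusters chosen on pre-post change.* Steps 1 to 3 apply directly.
- *Clusters chosen on the task contrast, both sessions weighted equally.* Simulated pre-post d was about 0.00, and the CI excluded zero in 4-5% of clusters: no bias.
- *Clusters chosen on baseline scans.* Regression to the mean creates false change. With no true change and an assumed between-session correlation of 0 to 0.5, pre-post d was 0.27-0.39 at task d 0.3 and 0.18-0.26 at task d 0.5. The CI excluded zero in 25-47% and 14-23% of clusters, against a nominal 5%. These come from a small simulation and are approximate.

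**The case against.** The strongest reply is that the harm needs a step the protocol does not write down. The fMRI section stops at extraction; it does not say that d, a CI or a p-value follows. The summary named there is means and SDs with group comparisons, and a SAP that is not shown may settle the rest. This stands in part. The harmful use is permitted, not stated.

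Second, the trial's questions are pre-post change and its association with MAIA change, while the selecting factor is condition with no time factor. If selection uses both sessions equally, pre-post change is not inflated, as Step 4 confirms. This stands as one of three readings. The text does not choose between them, and the other two are biased.

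Third, the secondary outcome in the hypotheses is worded as connectivity, while the cluster step concerns percent signal change. That is correct, but Aim 5 covers activity as well as connectivity.

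A reader might also infer something stronger: that the trial's main effect sizes are affected, and that the fMRI intervals almost never contain the truth. The documents do not support either. The hypotheses state that the task "is feasible and is acceptable to patients with chronic low back pain (cLBP) (Primary Outcome"), the power paragraph is built on pain impact, and no section makes fMRI the main result. Coverage fails badly only for small true effects at a strict threshold. At p<0.001 it is 84% at d = 0.5 and 96% or more at 0.8 and above.

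**Conclusion.** The point holds in limited form. The protocol states a circular extraction rule, and any d or interval for the selecting contrast taken from those clusters would be biased upward. The bias carries over to pre-post change if clusters are chosen on that change or on baseline alone.

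The size depends on a threshold the protocol does not give and on the true effect. With 27 completers it is material for small to moderate effects. It is minor for large ones: 1.04- to 1.18-fold at d of 0.8 to 1.0 across p<0.001 to p<0.01.

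The scope is the secondary and exploratory fMRI analyses. It is worth correcting before analysis, because the general effect-size sentence does not exclude fMRI and the remedy needs no new data.

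**What to change.** In the fMRI analysis section:

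1. State that signal extracted from surviving clusters is descriptive only, without d, CI or p-value.
2. Take any fMRI d and 95% CI, and the brain-change values correlated with MAIA change, from ROI masks fixed and listed before the data are seen, or from leave-one-subject-out clusters. The present text says only that ROIs are selected and uses them for the LASSO models, so both the timing and this added use must be written in.
3. Define condition, and state which contrast and which sessions select clusters, so that selection rests neither on baseline alone nor on the pre-post change being estimated.

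The cost is analysis wording and an early commitment to a list of regions; no new data or visits are needed. The reported fMRI effects will probably be smaller, and effects outside the chosen regions can only be described.

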*Single-subject Functional Analysis of Regional Activation Maps*: Average activation within each region will be subjected to regression analysis by way of LASSO. The LASSO regression model will be executed in R using the glmnet package for Lasso and Elastic-Net Regularized General Linear Models. LASSO will be performed on a single-subject basis to create subject specific models that best separate conditions of interest (e.g. high pain anticipation from low pain anticipation). Logistic regression methods such as LASSO allow for a smaller number of predictors to be included in the model, allowing the experimental pain task to be shortened and optimized. Regression will be then fit to the training set and will be optimized by cross-validating the model 100 times. This will allow for accurate and consistent discrimination between single-subject neurobiological patterns of different conditions. We can then apply these LASSO predictions on the test set (e.g., anticipation during uncertainty) at a probabilistic level, based on the correlation of the activation statistic to the cross-validated glmnet model. Thus, each participation can be labeled individually on the condition of interest.

**Qualitative Exit Interviews:**In-depth qualitative semi-structured interviews will be conducted after the final assessment. We will use the micro-phenomenology method by Petitmengin^3^ and probe the first-person experience in managing pain by either the narrative or the interoceptive awareness approach. This method has been developed to capture subjective processes in meditation and consciousness research (directed by Francisco Varela). It attempts to combine and mutually enlighten neural and experiential descriptions of cognitive processes and holds promise for providing additional heuristic information on the micro-phenomenology of interoceptive awareness and mind-body approaches in general. We will conduct 20 elicitation interviews in selected participants, 10 with strong (upper tercile) and 10 with weak (lower tercile) changes in pain impact outcomes.

References:

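### The single-subject LASSO plan concludes that every participant can be labelled, but its named test set has no true label and its cross-validation is used to optimise the model

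*Protocol*

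**What the plan says.** The relevant text is in the protocol, Analyses, under the heading on single-subject functional analysis of regional activation maps. The preceding paragraphs on task-based fMRI supply the data.

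- **Data.** The unit is the trial: "a separate regressor will be calculated for each anticipation and stimulation trial such that each event has its own estimated amplitude".
- **Training.** LASSO logistic regression is run within each participant to give "subject specific models that best separate conditions of interest (e.g. high pain anticipation from low pain anticipation"). The task design fixes these labels.
- **Tuning.** "Regression will be then fit to the training set and will be optimized by cross-validating the model 100 times".
- **Expected result.** "This will allow for accurate and consistent discrimination between single-subject neurobiological patterns of different conditions".
- **Application.** "We can then apply these LASSO predictions on the test set (e.g., anticipation during uncertainty) at a probabilistic level".
- **Conclusion.** "Thus, each participation can be labeled individually on the condition of interest". I read the second word after the comma as 'participant'.

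The section gives no number of trials or regions, no tuning criterion, no comparison with chance and no outcome for a participant whose model does not work.

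**The concern.** The section reasons from tuned, to accurate, to everyone can be labelled. Neither step follows.

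A test set normally holds observations whose true class is known and which were not used in fitting. Trials of uncertain anticipation have no high/low truth, so predictions on them cannot be scored. The labelled high/low trials can be scored, but the only cross-validation described on them is the one that optimises the model. The protocol names no separate estimate of accuracy.

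The label is thus a function of the activations and the fitted model alone. A participant whose regional activation does not separate high from low anticipation is processed like one whose activation separates them well, and the two kinds of label look alike in the output. At stake is whether individual labels can be interpreted, and whether the statement about accurate discrimination is put to a test it could fail.

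**Working it through.** **Plan's own figure.** The protocol states no accuracy, threshold or sample-size figure for this step, so there is nothing to reproduce.

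**What an empty model returns.** LASSO logistic regression minimises the average negative log-likelihood plus λ × Σ|β|. If every β is shrunk to zero, only the intercept remains: a = log[ȳ / (1 − ȳ)]. With balanced conditions ȳ = 0.5, so a = 0 and the predicted probability is 1 / (1 + e⁰) = 0.5 for every trial. That is not an informative label. The question is how often tuning keeps a non-empty model when there is no signal.

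**Assumed inputs.** 10 to 30 trials per condition, 10 to 30 regions, independent Gaussian noise, balanced conditions, 5-fold cross-validation. Repeats were cut from the stated 100 to 2 for run time. There were 80 simulated participants and 20 uncertain trials each. The penalty was chosen at minimum cross-validated deviance. The signal scenario shifted 3 regions by 1.2 SD.

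| Trials per condition, regions | Non-empty model, no signal | Mean CV accuracy, no signal (95th percentile) | Mean CV accuracy, signal |
|---|---|---|---|
| 10, 10 | 20% | 0.485 (0.71) | 0.774 |
| 10, 30 | 21% | 0.468 (0.70) | 0.717 |
| 20, 20 | 26% | 0.491 (0.66) | 0.802 |
| 30, 30 | 14% | 0.474 (0.60) | 0.808 |

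The Monte Carlo standard error of a proportion near 20% is √(0.2 × 0.8 / 80) = 0.045. Under the one-standard-error rule the non-empty share fell to 5-11%.

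**Sensitivity to the tuning criterion.** The protocol names none. Other pure-noise runs, with 20 or 40 labelled trials in total and 10 or 20 regions where recorded, gave:

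- Deviance tuning: non-empty model in 25-35%, and mean cross-validated accuracy of 48-50% where recorded.
- Accuracy tuning: non-empty model in 60-90% depending on penalty grid and repeats. Where recorded, mean tuned accuracy was 55-57%, and 28-38% of no-signal participants reached 60% or more.

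**Reading the results.** Cross-validated accuracy on labelled trials separates signal (0.72-0.81) from none (0.47-0.49) on average. For a single participant it is weaker, since 0.60-0.71 lies within chance. So a per-participant comparison with chance is needed before a label is read.

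**How large that comparison is.** For n independent held-out labelled trials, take the smallest k with P(X ≥ k | n, 0.5) ≤ 0.05:

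- n = 20: k = 15 (75%)
- n = 40: k = 26 (65%)
- n = 60: k = 37 (62%)

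**The case against.** **A reader might infer that the promised discrimination cannot be checked at all.** The text does not support that. The accuracy sentence follows the cross-validation sentence and concerns the trained conditions, whose labels are known. Out-of-fold accuracy there is a check that can fail. It is optimistic only to the extent that the same folds choose the penalty, and the upward shift in mean accuracy appeared clearly only when accuracy was the tuning criterion. What cannot be checked is accuracy on the uncertain trials.

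**A reader might infer that every no-signal participant gets a definite label.** The wording is that participants can be labelled, and predictions are probabilistic. An empty model returns 0.5, so a label for everyone would require forcing that value to one side.

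**A reader might measure the problem by how lopsidedly the uncertain trials split.** The protocol has no majority rule. Fair coin flips split at least 60/40 in 50% of cases with 20 trials and 75% with 10, so such a count says little.

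**A reader might fear contaminated pre-post or MAIA comparisons.** No section enters these labels into one. Aim 5 uses changes in brain activity and connectivity, and the group model uses percent signal change.

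**Applying a trained model to an ambiguous condition is legitimate, the condition is given only as an example, and thresholds may sit in a statistical analysis plan that is not shown.** All of this stands. It does not rescue what the protocol itself states: a condition without truth is called a test set, and tuning is offered as the ground for labelling everyone. A later plan that left some participants unclassified would depart from that sentence.

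**Conclusion.** The point holds as a limited one. The inference from a tuned model to accurate discrimination and a label for each participant is not supported by the steps described. A participant without signal can receive an informative-looking label: roughly 15-35% of such participants under deviance tuning, more under accuracy tuning, and fewer under the one-standard-error rule. These shares rest on assumed trial and region counts, independent Gaussian noise, far fewer cross-validation repeats than the stated 100, and no more than about 100 simulated participants per setting where recorded. They show that the problem is not negligible; they do not predict this study's error rate.

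The study describes itself as proof of concept without rigorous hypothesis testing, and the labels feed no named endpoint. The consequence is confined to how the individual fMRI labels may be read.

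**What to change.** 1. Estimate each participant's accuracy on the labelled high/low trials by nested cross-validation: choose the penalty in the inner folds and score in outer folds not used for tuning.
2. Report that accuracy against a null distribution from permuting trial labels within the participant.
3. Call the uncertain-anticipation trials an application set, not a test set.
4. Replace the sentence that each participant can be labelled with one saying that labels are interpreted only alongside that accuracy. Flag participants not distinguishable from chance as 'not classifiable', and show results with and without them.

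Flagging is preferable to outright exclusion. With 20 labelled trials and the 15/20 requirement, a participant whose true accuracy is 0.72 would pass only about 50% of the time (84% at 0.81), so a hard rule would discard real signal from a sample of 30. Dropping participants separately at each visit could also bring selection into any pre-post use of the labels.

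The cost is analysis code and computing time, with no new scans. The downside is that some participants will have no interpretable label.
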